## Abstract

**Background:**

Patient education on pharmacological therapy may increase medication adherence and decrease hospitalizations. Our aim is to evaluate the effectiveness of pharmaceutical care at emergency department discharge in patients with hypertension and/or diabetes.

**Methods/design:**

This is a randomized controlled trial. Participants will be recruited from a public emergency department at Restinga district in Porto Alegre, southern Brazil. A total of 380 patients will be randomly assigned into 2 groups at the moment of emergency department discharge after receiving medical orientations: an intervention group, consisting of a structured individual counseling session by a pharmacist in addition to written orientations, or a control group, consisting only of written information about the disease. Outcomes will be assessed in an ambulatory visit 2 months after the randomization. The primary outcome is the proportion of patients with high medication adherence assessed using the Morisky-Green Test and the Brief Medication Questionnaire. The secondary outcomes are reduction of blood pressure, glycated hemoglobin, fasting plasma glucose, quality of life and number of visits to the emergency department.

**Discussion:**

Pharmaceutical care interventions have shown to be feasible and effective in increasing medication adherence in both hospital outpatient and community pharmacy settings. However, there have been no previous assessments of the effectiveness of pharmacy care interventions initiated in patients discharged from emergency departments. Our hypothesis is that pharmaceutical counseling is also effective in this population.

**Trial registration:**

ClinicalTrials.gov registration number: NCT01978925 (11 November 2013) and Brazilian Registry of Clinical Trials U1111-1149-8922 (5 November 2013).

**Electronic supplementary material:**

The online version of this article (doi:10.1186/s13063-015-0579-3) contains supplementary material, which is available to authorized users.

## Background

Cardiovascular disease (CVD) is the leading cause of mortality and burden of disease as measured in disability-adjusted life years (DALYs). Globally, high blood pressure and high blood glucose alone are responsible for 13% and 6% of deaths, respectively [1].

Treatment of chronic diseases commonly includes the long-term use of pharmacotherapy. Despite the efficacy of these treatments, inadequate medication adherence has been reported to approximately 50% of patients. Low adherence reduces the effectiveness of treatment, resulting in suboptimal illness control. As a consequence, an increased use of healthcare resources and reduction in patients’ quality of life has been observed [2-5]. About 20% of hospitalized patients experience adverse events after discharge. However, it is estimated that 60% of these events could be prevented with the proper use of medications [6-9].

Interventions focused on patient education related to pharmacological therapy may increase medication adherence and decrease morbidity [10]. Several interventions for improving adherence have been tested in clinical studies, including motivational and behavior strategies, simplification of dosing regimens, unit dose packaging, educational counseling, refill reminders and self-monitoring [11-16]. A systematic review of studies assessing interventions to improve medication adherence has shown an overall increase of 4 to 11%; however, no single strategy appeared to be superior [9].

Pharmaceutical care interventions for improving medication adherence seem to be feasible and effective, both in hospital and in community pharmacy settings [17,18]. Clinical pharmacists are able to identify and intervene to prevent potential problems with prescriptions written prior to discharge from the hospital, and studies have suggested that discharge counseling is able to improve medication adherence [19]. However, there is no evidence in the literature regarding the effectiveness of pharmaceutical care interventions initiated in patients discharged from emergency departaments (ED). In addition, few studies have assessed the impact of these interventions in developing countries, and the effect of these interventions in populations with lower income and educational level is uncertain.

The aim of this study is to compare pharmaceutical care at discharge from the ED with usual care in the adherence to medication prescriptions and in the control of hypertension and/or diabetes.

## Methods/design

### Study design

This is a randomized controlled, single-center study, with blinding of outcome assessors. A pilot study with ten patients was previously conducted in order to test study logistics and data collection instruments. Participants will be recruited from a public ED at Restinga district in Porto Alegre, southern Brazil. Porto Alegre is the 10th largest city in Brazil, with 1.5 million inhabitants. Restinga is a low-income district of Porto Alegre, with approximately 100,000 people and a Human Development Index (HDI) of 0.700 to 0.799, whereas Porto Alegre HDI ranges from 0.700 to 0.977 [20]. This ED is the single reference emergency service of the southern region of Porto Alegre, with 8,000 visits monthly. Eligible participants will be randomized to either the intervention or the control group, and will complete a follow-up interview after a period of 2 months (Figure 1).

**Figure 1 Fig1:**
[figure not shown]
**Flow diagram of the study design.** *Questionnaires: sociodemographic variables; comorbidities; medication adherence; physical activity; alcohol consumption. ^‡^For patients with hypertension. ^†^For patients with diabetes. ^††^Anthropometrical assessment: weight, height, waist and hip circumferences. BP = blood pressure; CPG = capillary plasma glucose; HbA1c = glycated hemoglobin.

### Inclusion and exclusion criteria

All patients with ED discharge from 8 am to 6 pm, on weekdays, will be screened for eligibility.

#### Inclusion criteria

age ≥ 18 years;previous diagnosis and drug treatment for hypertension and/or diabetes;inadequate blood pressure (BP) control (systolic BP ≥ 160 mmHg or diastolic BP ≥ 100 mmHg), inadequate diabetes control (capillary plasma glucose ≥ 200 mg/dL) or moderate/severe hypoglycemia (capillary plasma glucose < 70 mg/dL associated with symptoms or clinical signs).

#### Exclusion criteria

patients without a prescription list or not able to report medications in use;patients not residing in the city of Porto Alegre;patients unable to answer the questionnaire or to sign the informed consent form;patients forwarded to hospitalization.

### Study conduct

Eligible participants will be identified through active screening by a research assistant, reviewing medical notes of admitted patients. The research assistant will describe the project to each potential participant, will provide a straightforward language statement and will invite them to participate in the study. If the participant accepts, written informed consent will be sought before baseline interview and physical examination. All participants will be referred to the study pharmacist for randomization after baseline data collection.

### Baseline measures

Data collection at baseline includes measurement of BP (for patients with hypertension), glycated hemoglobin (HbA1c) and fasting plasma glucose (for patients with diabetes). In addition, medication in use, socio-demographic, comorbidity and anthropometrical variables (for example, gender, age, ethnicity, marital and smoking status, alcohol consumption, physical activity, circumferences and body mass index) will be recorded. The medical prescription at discharge will also be documented.

### Randomization and participants allocation

Following baseline data collection, eligible participants will be randomized to either the intervention or the control group in a 1:1 ratio, using a telephonic central for allocation concealment. The randomization sequence will be generated by using a computer program in blocks of four, six and eight. Randomization will be stratified according to the number of different medications in use (<5 or ≥ 5).

### Pharmaceutical care group

In the ED, immediately after discharge, participants randomized to the pharmaceutical care group will receive intervention coordinated by the study pharmacist. The clinical pharmacist will provide a structured 30-minute intervention for enhancing their medication adherence.

The recommendations include: discussion on hypertension and/or diabetes, risk of complications, prescribed drug therapy, correct use of medications and proper dosage, possible adverse effects, route of administration, schedule of administration and correct storage. The pharmacist will also emphasize the importance of lifestyle modifications. Printed educational material, with information on hypertension and/or diabetes medications, including suggested lifestyle interventions (for example, reduce salt and sugar intake, practice regular physical activity, smoking cessation, reducing alcohol consumption, monitor stress levels in day-to-day and reduce weight and keep it within the normal range) was prepared to assist in the intervention and will be handed to patients in the end of the session.

### Control group

In addition to counseling provided by a physician and by the nursing staff during their stay in the ED (usual care), patients randomized to the control group will receive the same printed material information on hypertension and/or diabetes medications and lifestyle interventions in order to keep patients masked.

### Follow-up visit

An ambulatory follow-up visit will occur 2 months after randomization for the assessment of the study’s outcomes. We will contact participants by phone prior to the follow-up visit in order to minimize losses; if necessary, home visits will be performed for those without conditions to attend the follow-up visit in the clinic. Data will be collected by a research assistant who is unaware of the randomization status.

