### Secondary endpoints

The secondary outcomes are:systolic and diastolic BP, for patients with diagnosis of hypertension;HbA1c and fasting plasma glucose, for patients with diagnosis of diabetes;quality of life, assessed by the the EuroQol five-dimension (EQ-5D) instrument [23,24];number of visits to the ED.

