### Sample size

The sample size was estimated assuming a percentage of 50% nonadherence to the medication treatment in the control group [25]. To detect a 15% absolute increase in the medication adherence in the intervention group, a sample size of 190 participants will be needed in each group, considering an alpha error of 5% (bilateral), statistical power of 80% and 10% of losses to follow-up.

One of the researchers of the study will be responsible for quality control of the collected information. The participants will be randomly selected to answer a simplified questionnaire containing key issues by telephone. This control will be performed in 10% of the sample.

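### ED visits are tied to the 2-month follow-up visit, so patients finally lost have no count, although the recruiting ED's own records could cover everyone randomized

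*Protocol article*

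**What the plan says.** The Abstract (Methods/design) states: "Outcomes will be assessed in an ambulatory visit 2 months after the randomization". The Follow-up visit section repeats this: "An ambulatory follow-up visit will occur 2 months after randomization", and gives outcome assessment as the visit's purpose. Study design calls the same contact an interview. Secondary endpoints lists "number of visits to the ED" without a data source or counting window.

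Follow-up visit also provides for phone contact beforehand, home visits for patients who cannot come to the clinic, and a research assistant unaware of allocation. Sample size allows for losses: "considering an alpha error of 5% (bilateral), statistical power of 80% and 10% of losses to follow-up".

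Data analysis commits all analyses to intention to treat. It gives a missing-data scenario for the primary outcome and restricts continuous outcomes, with blood pressure and glucose as examples, to patients seen at follow-up. It states no rule for ED visits.

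On the setting, Study design says: "This ED is the single reference emergency service of the southern region of Porto Alegre, with 8,000 visits monthly". Study conduct has a research assistant reviewing medical notes there to find eligible patients.

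**The concern.** Blood pressure, HbA1c and questionnaires need the patient to be present. A count of ED visits does not. Tying it to the follow-up contact gives it the same missing data as the other outcomes without need.

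The missing data may also be informative. A patient who deteriorates, is admitted or dies may have more ED visits and be harder to reach at 2 months. If loss differs between arms, a comparison among patients seen is biased, and the arm that loses more patients looks better.

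Reporting is a second, weaker issue. If the count comes from the interview, the patient supplies it. Only the intervention arm has the 30-minute pharmacist session, so reporting could differ by arm even though the assessor is blinded.

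**Working it through.** **1. The plan's own figure.** No sample size or event rate is given for ED visits, so the only figure to reproduce is the one for the primary outcome. Inputs are in Sample size: "assuming a percentage of 50% nonadherence to the medication treatment in the control group"; a 15-point difference, hence 50% against 65% adherent; two-sided alpha 0.05; power 80%; 10% loss.

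n per arm = [1.96·√(2·0.575·0.425) + 0.842·√(0.50·0.50 + 0.65·0.35)]² / 0.15² ≈ 169.3, rounded up to 170.

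Inflated for loss: 170/0.90 = 188.9, rounded up to 189. The stated 190 per group is reproduced, and the point below does not touch it.

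**2. Patients without a count.** At the planned loss, 0.10 × 380 = 38 patients have no ED-visit count and 342 do. From numbers alone the standard error rises by √(380/342) = 1.054, about 5%. Lost precision is minor; the issue is possible bias.

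**3. Illustrative bias.** All rates here are assumptions. Let the true mean be 0.5 visits per patient in both arms (no effect), with a mean of 1.0 among those lost. If a fraction L is lost, the mean among patients seen is

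(0.5 − L × 1.0) / (1 − L).

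| Loss, arm A / arm B | Mean seen, A | Mean seen, B | Ratio B/A | Difference B − A |
|---|---|---|---|---|
| 10% / 10% | 0.400/0.900 = 0.444 | 0.444 | 1.00 | 0.000 |
| 7.5% / 12.5% | 0.425/0.925 = 0.459 | 0.375/0.875 = 0.429 | 0.93 | −0.031 |
| 5% / 15% | 0.450/0.950 = 0.474 | 0.350/0.850 = 0.412 | 0.87 | −0.062 |

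Each row averages 10% loss, as planned. A complete record count would give 1.00 throughout.

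**4. Other assumed rates.** Let patients seen average 0.3 visits in both arms and lost patients 0.3 to 0.9. With 5% against 15% loss and 0.9 in those lost, the true arm means are 0.95·0.3 + 0.05·0.9 = 0.33 and 0.85·0.3 + 0.15·0.9 = 0.39. A difference of 0.06 would be missed. With 0.3 in those lost, nothing is missed.

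**5. Bias against random error.** In the 5%/15% row, the visits counted are 190·0.5 − 9.5·1.0 = 85.5 and 190·0.5 − 28.5·1.0 = 66.5. The Poisson standard error of the log ratio is √(1/85.5 + 1/66.5) = 0.16, and log(0.87) = −0.14. Even this scenario shifts the estimate by slightly less than one standard error.

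**The case against.** The strongest reply is that a journal article may leave the data source of one secondary count to the full protocol. Silence on the source would not be a finding by itself. But the article is not silent on ascertainment: it places all outcomes at the 2-month contact, and for this outcome that route is weaker than one already at hand.

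A reader might go further on several points, and the documents do not support it:

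- **That the count rests on recall.** No source is stated, and a records check around the visit is not excluded. The interview wording only makes self-report the natural reading.
- **That everyone who misses the clinic visit is uncounted.** Phone contact and home visits reduce this to the patients finally lost.
- **That patients are unmasked.** The Control group section gives both arms the same printed material so that patients stay masked. One may doubt that a shared leaflet conceals a 30-minute session, but that is a judgement.
- **That loss will differ by arm.** Nothing in the documents predicts this. With equal loss and equal rates among those lost, the illustrated bias vanishes.
- **That the trial's policy value depends on service use.** The hypothesis in the Discussion concerns adherence and disease control. Service use appears as a consequence of poor adherence and in the results of earlier studies.
- **That records would capture every visit.** The ED serves the southern region, while the exclusion criteria admit residents of the whole city. The documents also do not show that return visits can be searched retrospectively; they describe note review for screening only.

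The last item limits the remedy but does not remove its advantage.

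**Conclusion.** The point holds for one secondary outcome. Under the stated route, patients finally lost have no ED-visit count, about 38 of 380 at the planned rate, and that loss may be related to the outcome. Differential reporting by arm is possible but rests on inference.

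The bias cannot be sized from the documents. Under the main assumptions it runs from none (ratio 1.00, equal loss) through 0.93 to 0.87 (5% against 15% loss). These figures show what could happen and are not a forecast. The change is worth making because it is cheap and the outcome does not require the patient's presence.

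**What to change.** State the source and window for this outcome. Count ED visits in the 2 months after randomization from the recruiting ED's records, extracted blind to arm, for all 380 randomized participants, and analyze everyone as randomized. Ask about visits to other EDs at the follow-up interview and report them as a supplementary count.

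The cost is a record look-up for 380 patients and a short protocol addition, after confirming that return visits can be retrieved by patient. The drawback is that the record count omits visits elsewhere; the supplementary count indicates how many, among patients interviewed.

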### Primary endpoint

The primary outcome is the proportion of patients with high medication adherence at 2 months. Medication adherence will be assessed subjectively using two validated questionnaires in the Portuguese language: the Morisky-Green Test (MGT) and Brief Medication Questionnaire (BMQ) [21,22]. The MGT assesses both intentional and unintentional nonadherence and comprises four items. Responses for each item are scored one for ‘yes’ and zero for ‘no’ and are added together. A total score of zero represents good adherence and a score of one or more represents suboptimal adherence. The BMQ is composed of eleven questions, divided into three domains (regime, beliefs and memory).

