### Data analysis

The questionnaires will be entered into the database through processing by optical reader, using the Remark Office OMR® Software (version 8.0 Gravic, Inc., Malvern, PA) . All analyses will follow the intention-to-treat (ITT) principle. For the primary outcome, we will initially consider in the analysis patients with complete follow-up. A secondary analysis will be performed with data of all patients initially randomized, considering, as the worst plausible scenario, that 29% of the losses to follow-up, in both groups, are adherent. The worst plausible scenario was based on a previous observational study, conducted in 2012 in the same region, showing that 34.5% (95% confidence intervals (CI), 29% to 40%) of patients with hypertension assisted in basic health units are adherent according to the same instrument [26]. We will not use any imputation method for continuous outcomes, such as BP and blood glucose. For these outcomes, we will include only those participants who attended the follow-up visit.

Data will be presented as relative risk (RR) and mean difference (MD), with 95% CI. Categorical variables will be compared using the chi-square test; continuous variables will be compared using the Student *t-*test or the Mann–Whitney *U-*test. The analysis will be conducted in SPSS for Windows (version 19.0, Redmond, WA, USA) and Stata (version 10, College Station, TX, USA); the statistician will be blinded for the randomization status.

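### One primary outcome is measured by two unranked questionnaires, so the stated 5% alpha and 80% power are assured only if one of them is named as deciding

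*Protocol article*

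**What the plan says.** The Primary endpoint section of the protocol article states a single outcome: "The primary outcome is the proportion of patients with high medication adherence at 2 months". It then names two instruments for it: "Medication adherence will be assessed subjectively using two validated questionnaires in the Portuguese language: the Morisky-Green Test (MGT) and Brief Medication Questionnaire (BMQ". The abstract's Methods/design paragraph does the same: "The primary outcome is the proportion of patients with high medication adherence assessed using the Morisky-Green Test and the Brief Medication Questionnaire". No sentence ranks the questionnaires, combines them into one patient-level classification, or divides alpha between them. The Secondary endpoints section does not list the BMQ, so it cannot be read as a supportive measure.

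For the MGT there is a threshold: "A total score of zero represents good adherence and a score of one or more represents suboptimal adherence". The label is good adherence, whereas the outcome speaks of high adherence. For the BMQ there is only a description: "The BMQ is composed of eleven questions, divided into three domains (regime, beliefs and memory".

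The Sample size section gives one control rate, without an instrument: "The sample size was estimated assuming a percentage of 50% nonadherence to the medication treatment in the control group". It looks for a 15-point absolute increase, "considering an alpha error of 5% (bilateral), statistical power of 80% and 10% of losses to follow-up". The Data analysis section compares categorical variables by chi-square. It bases its worst plausible scenario for losses (29% adherent) on the lower confidence limit from an earlier study in which 34.5% of patients "are adherent according to the same instrument". The word is singular and the instrument is not named.

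**The concern.** The sections do not fit together. The outcome is one proportion, the sample size is for one test, and the missing-data scenario rests on one instrument, but two questionnaires feed the outcome. An analyst following the text could test each of them at 5% and would have no rule for a split result. The deciding questionnaire could then be chosen after the results are seen, and the stated error rate would no longer protect the trial's main conclusion. Nor can a reader tell which questionnaire the 50%, 34.5% and 29% figures describe, and so whether they suit the outcome that will be tested.

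**Working it through.** **Inputs from the article.** Control adherence is 50% (one minus 50% nonadherence), intervention adherence 65%, alpha 5% two-sided, power 80% and losses 10% (Sample size). Allocation is 1:1 (Randomization). The primary analysis uses patients with complete follow-up (Data analysis), which is 190 × 0.9 = 171 per arm.

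**Inputs assumed.** The article gives no correlation between the MGT and BMQ test statistics, so ρ is varied from 0 to 0.9. It gives no separate rates per instrument, so 50% versus 65% is used for each.

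**1. The plan's own figure.** Pooled two-proportion formula, mean rate 0.575, no continuity correction:

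n = [1.96·√(2 × 0.575 × 0.425) + 0.8416·√(0.50 × 0.50 + 0.65 × 0.35)]² / 0.15² = (1.370 + 0.582)² / 0.0225 ≈ 169.3, so 170 per arm.

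170 / 0.9 = 188.9, so 189, against 190 stated. This reproduces. Power with 171 per arm is Φ[(0.15·√171 − 1.370) / 0.691] = Φ(0.856) = 80.4%. The sample size is therefore right for exactly one binary comparison.

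**2. Two tests at 5% each.** With the two statistics bivariate normal:

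- Success on either: false-positive rate = 1 − P(|Z1| < 1.96 and |Z2| < 1.96). At ρ = 0 this is 1 − 0.95² = 9.75%.
- Success on both: power = P(both significant), with 80.4% marginal power. At ρ = 0 this is 0.804² = 64.6%.

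| ρ (assumed) | Either: false-positive rate | Both: power at 171 per arm | Both: randomized per group for 80% power |
|---|---|---|---|
| 0 | 9.75% | 64.6% | 247 |
| 0.3 | 9.5% | 67.2% | 242 |
| 0.5 | 9.1% | 69.3% | 235 |
| 0.7 | 8.4% | 71.8% | 226 |
| 0.9 | 7.0% | 75.4% | 212 |

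The two rules do not fail in the same way. Under the either rule the chance of at least one success is 2 × 80.4% minus the joint power, about 85% to 96%, so only alpha is lost. Under the both rule alpha stays at or below 5%, so only power is lost.

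**3. One patient-level composite.** This is one variable and one test, so alpha stays at 5%. With rate q on each instrument and within-patient correlation φ (assumed equal in both arms), the proportion adherent on both is q² + φq(1 − q), and the proportion adherent on at least one is 1 − [(1 − q)² + φq(1 − q)].

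| Composite | φ | Control vs intervention | Power at 171 per arm |
|---|---|---|---|
| Adherent on both | 0 | 25.0% vs 42.3% | 92.5% |
| Adherent on both | 0.7 | 42.5% vs 58.2% | 82.9% |
| Adherent on at least one | 0 | 75.0% vs 87.8% | 86.1% |
| Adherent on at least one | 0.7 | 57.5% vs 71.8% | 79.4% |

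Power may be adequate, but neither the control rate nor the difference is the one in the Sample size section.

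**4. Both kept as primary with Bonferroni.** At 2.5% each the critical value is 2.241. Power per test is Φ[(0.15·√171 − 2.241 × 0.699) / 0.691] = Φ(0.571) = 71.6%. Reaching 80% per test needs 206 evaluable, or 206 / 0.9 ≈ 229 randomized, per group (458 in total).

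**5. One instrument named, other base rates.** With a 15-point difference and 171 per arm, power is 82.4% from a control rate of 29%, 80.5% from 34.5% and 79.6% from 40%. Naming one instrument therefore keeps the planned size workable over these base rates, provided the 15-point effect applies to it.

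**The case against.** A reader might infer that the stated alpha and power simply do not hold. The article does not support that. It speaks of one proportion, and its sample size is right for one test. If one instrument decides, as the singular wording in the Data analysis section may suggest, both figures stand. A single patient-level composite is also a possible reading and would keep alpha at 5%. It is likewise too strong to say that the trial is bound to produce two primary results, or that alpha and power would both fail: each unadjusted rule breaks only one of them.

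A second tempting reading is that the absent BMQ threshold is an error in itself. This is a journal article that cites validated instruments, and scoring detail may lie in a full protocol or analysis plan that is not shown. Taken alone, that absence is not a finding.

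Third, the sizes above rest on assumed correlations and on equal rates for both instruments. They illustrate possible rules and do not estimate this trial's error rates.

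All three objections stand, and they limit the consequence. They do not remove the defect. The article has its own primary endpoint section, and it fixes alpha, power, test and missing-data scenario for one comparison while naming two unranked measures. That is a primary outcome fixed badly, and not merely detail deferred to another document.

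**Conclusion.** The point holds in conditional form. The primary outcome has no deciding rule, so the 5% alpha and 80% power belong to a test that the article does not identify. They are assured if one instrument is prespecified as deciding. Without adjustment, an either rule would put the false-positive rate at about 7.0% to 9.75%. A both rule would put power at about 65% to 75%, with alpha held. A composite would hold alpha but would need its own control rate and effect. The ambiguity itself is read directly from the text and needs no assumption. The sizes depend on the assumed correlations and, for power, on 50% versus 65% applying to each questionnaire. Because this is the primary outcome, it should be settled before the data are analysed.

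**What to change.** - In the abstract and the Primary endpoint section, name one deciding instrument and its cut-off at 2 months, tested once at two-sided 5%. An MGT score of zero is the natural choice, as the only threshold stated, unless the 50% and 34.5%/29% figures turn out to come from the BMQ. Use one label for the category, high or good.
- List the other questionnaire under Secondary endpoints as an adherence outcome with its own cut-off.
- In Sample size and Data analysis, state which instrument the 50%, 34.5% and 29% figures actually come from, and align them with the chosen primary. The article does not show this, so it has to be checked in the cited sources and not simply declared.
- If both are to stay primary, prespecify the rule and restate the power: Bonferroni at 2.5% each gives about 72% per test at 171 per arm, and 80% per test needs about 229 randomized per group.

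Cost: with one named instrument the sample size stays at 190 per group and no further data are needed. One questionnaire loses primary status. Because the trial is registered and recruiting, the protocol and both registry entries need an amendment. Keeping both as primary means accepting lower power or enrolling more patients.
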